## Abstract

**Background:**

The main hypothesis of this study is that Oxpentifylline administration will effectively treat erythropoietin- or darbepoietin-resistant anaemia in chronic kidney disease patients.

**Methods/design:**

Inclusion criteria are adult patients with stage 4 or 5 chronic kidney disease (including dialysis patients) with significant anaemia (haemoglobin ≤ 110 g/L) for at least 3 months for which there is no clear identifiable cause and that is unresponsive to large doses of either erythropoietin (≥ 200 IU/kg/week) or darbepoetin (≥ 1 μg/kg/week). Patients will be randomized 1:1 to receive either placebo (1 tablet daily) or oxpentifylline (400 mg daily) per os for a period of 4 months. During this 4 month study period, haemoglobin measurements will be performed monthly. The primary outcome measure will be the difference in haemoglobin level between the 2 groups at the end of the 4 month study period, adjusted for baseline values. Secondary outcome measures will include erythropoiesis stimulating agent dosage, Key's index (erythropoiesis stimulating agent dosage divided by haemoglobin concentration), and blood transfusion requirement.

**Discussion:**

This investigator-initiated multicentre study has been designed to provide evidence to help nephrologists and their chronic kidney disease patients determine whether oxpentifylline represents a safe and effective strategy for treating erythropoiesis stimulating agent resistance in chronic kidney disease.

**Trial Registration:**

Australian New Zealand Clinical Trials Registry Number ACTRN12608000199314.

## Background

The development of erythropoiesis stimulatory agents (ESA), such as recombinant human erythropoietin (EPO) and darbepoetin alpha (DPO), has resulted in substantial health benefits for patients with end-stage kidney disease (ESKD), including improved quality of life, reduced blood transfusion requirements, decreased left ventricular mass, diminished sleep disturbance and enhanced exercise capacity [1,2]. Unfortunately, a considerable proportion of such patients exhibit a suboptimal haematologic response to ESA, which in most cases is due to inadequate iron supply to the erythron [3]. Other known causes of ESA-resistance include infection, neoplasia, severe hyperparathyroidism, aluminium intoxication, vitamin B_12 _deficiency, folate deficiency, inadequate dialysis, myelosuppressive agents, haemoglobinopathies, myelodysplasia and antibody-mediated pure red cell aplasia [4]. However, even after exclusion of these conditions, a significant minority (approximately 10%) of patients exhibit ESA-resistant anaemia and have been shown to have greatly increased morbidity and mortality [4]. Inhibition of erythropoiesis by cytokines, such as tumour necrosis factor-α (TNF-α) and interferon-γ (IFN-γ) may play an important role in these patients [5].

Although there is no currently effective treatment for patients with ESA-resistant anaemia, oxpentifylline (pentoxifylline) may represent a promising novel therapeutic strategy. Oxpentifylline has been used for more than twenty years in the treatment of peripheral and cerebral vascular diseases because of its potent haemorrheological properties, which include preservation of erythrocyte water and cation content [6,7]. The drug has subsequently been found to exhibit important anti-inflammatory properties, including anti-apoptotic, anti-oxidant, anti-TNF-α and anti-IFN-γ actions [8-11]. These actions appear to be mediated via inhibition of phosphodiesterase [12]. Two small, prospective, non-randomized studies have demonstrated that oxpentifylline may significantly improve haemoglobin levels in chronic kidney disease patients with ESA-resistant anaemia (vide infra) [13,14] Navarro et al [14] treated 7 anaemic patients with advanced chronic kidney disease (CKD) (creatinine clearance < 30 mL/min) with oxpentifylline (400 mg daily per os) for 6 months. Haemoglobin levels significantly increased from 99 ± 5 to 106 ± 6 g/L (p < 0.01), whilst serum TNF-α concentrations decreased from 623 ± 366 to 562 ± 358 pg/ml (p < 0.01). No changes were observed in untreated controls. Similarly, Cooper and associates [13] administered oxpentifylline (400 mg daily per os) for 4 months to 16 ESKD patients with EPO-resistant anaemia (defined as a haemoglobin level < 107 g/L for 6 months before treatment and an EPO dose ≥ 12,000 IU/week). Among the 12 patients who completed the study, mean haemoglobin concentration increased from 95 ± 9 to 117 ± 10 g/L (p = 0.0001), whilst *ex vivo *T cell generation of TNF-α and IFN-γ were significantly reduced.

Hepcidin may also play a role in ESA-resistant anaemia. This agent is produced by hepatocytes and secreted into the blood in response to iron status, anaemia, hypoxia and pro-inflammatory cytokines, especially IL-6 [15-17] and IL-1 [18]. Recently published data suggests that hepcidin binds to ferroportin (FPN1), a cellular iron exporter, resulting in internalisation and loss of function [19]. FPN1 is highly expressed in macrophages of the reticuloendothelial system and enterocytes in the duodenum and mediates iron release. In macrophages, the binding of hepcidin to FPN1 and its subsequent internalisation would result in iron accumulation within the cell and less release of iron. Patients with CKD may have elevated levels of IL-1, IL-6 and TNF-α [20,21]. It is possible that elevated levels of these cytokines in CKD increase hepcidin production and reduce iron release from macrophages in the bone marrow resulting in reduced availability of iron for erythropoiesis. In fact, prohepcidin was found to accumulate in renal insufficiency [22,23].

In most signaling pathways involving TNF-α and IL-6, IL-6 is a downstream component from TNF via nuclear factor kappa B [24]. Thus, interference with TNF-α production can interfere with IL-6 signalling. In experimental models, oxpentifylline has been shown to reduce IL-6 expression [25-27].

The available studies suggest that oxpentifylline may represent a significant advance in the treatment of ESA-resistant anaemia in chronic kidney disease, but they are limited by their lack of adequate controls and the associated potential for selection, observer and co-intervention biases. A prospective, randomized, double-blind, placebo-controlled trial is required to definitively test the hypothesis that oxpentifylline corrects ESA-resistant anaemia in chronic kidney patients. This study also offers the opportunity to explore the role of the novel peptide, hepcidin, as a possible mediator of iron availability and ESA-resistance.

## Methods/design

Ethics approval for the **H**emoglobin elevation in **E**rythropoietin **R**esistance with **O**xpentifylline (HERO) trial has been obtained from the local Institutional Ethics Committee in all participating centres prior to study initiation and patient enrolment. The study will be performed in accordance with the 2000 Edinburgh, Scotland Revision of the Declaration of Helsinki, the National Health and Medical Research Committee (NHMRC) Statement on Human Experimentation, Joint NHMRC/AVCC Statement and Guidelines on Research Practice, applicable ICH guidelines and the Therapeutic Goods Administration (TGA) – Note for guidance on good clinical practice (CPMP/ICH/135/95) annotated with TGA. Application under the Clinical Trials Notification (CTN) scheme will be required for this protocol.

### Participants

The study population includes adults (18 years or over) with stage 4 or 5 CKD (on dialysis or estimated GFR < 30 ml/min/1.73 m^2^) who are able to give informed consent and who have a haemoglobin concentration < 110 g/L for at least 3 months in spite of EPO dosage ≥ 200 IU/kg/week or DPO dosage ≥ 1 μg/kg/week for at least 1 month. Patients will be recruited by local investigators from participating renal units (outpatients and dialysis units) throughout Australia and New Zealand. The multicentre nature of the study will greatly enhance the generalisability of the trial.

Exclusion criteria include:

1. Patients with a history of psychological illness or condition which interferes with their ability to understand or comply with the requirements of the study.

2. Pregnancy or breast-feeding.

3. Known hypersensitivity to, or intolerance of, oxpentifylline or other methylxanthines, such as caffeine, theophylline or theobromine.

4. Active peptic ulcer disease.

5. Absolute or functional iron deficiency (ferritin < 100 μg/L and/or transferrin saturation < 20%).

6. Vitamin B_12 _or folate deficiency.

7. Parathyroid hormone level > 100 pmol/L.

8. Serum aluminium > 2 μmol/L.

9. Urea reduction ratio < 65% or single pool Kt/V < 1.0 (haemodialysis patients) or total weekly Kt/V < 1.7 (peritoneal dialysis patients).

10. Presence of systemic haematological disease (including antibody-mediated pure red cell aplasia) or known haemoglobinopathy

11. Major surgery, infection, acute myocardial infarction or malignancy within the last 3 months.

12. Melatonin treatment, androgen therapy or blood transfusion within the previous month.

13. Vitamin C therapy at dose greater than 100 mg/day or at a dose which has changed within the last 3 months.

14 Haemorrhagic stroke or severe haemorrhage within the last 3 months.

### Study design

The study is an investigator-initiated, prospective, double-blind, randomized, placebo-controlled phase 3 trial. Patients will be randomised to one of two treatment groups in equal proportion (Fig. 1). To ensure adequate concealment of allocation, the randomization will be performed using a central computer and web-based link to the central database provided through the Australasian Kidney Trials Network (AKTN). Patients will be randomized in permuted blocks with stratification for centre and disease stage/dialysis type.

**Figure 1 F1:**
[figure not shown]
Schema for the HERO Trial.

### Experimental intervention

The experimental intervention will be oxpentifylline (400 mg daily per os; Trental^®^, Sanofi-Aventis, Sydney, Australia). Oxpentifylline is registered in Australia for treatment of intermittent claudication on the basis of chronic arterial occlusive disease of the limbs. The standard dose is 400 mg three times daily. The dose of oxpentifylline selected for this study (400 mg daily) is lower than the standard dose because the drug may accumulate in renal failure. Moreover, this dose has been shown to be efficacious without significant side effects in 23 ESKD patients studied by Cooper et al [13] and Navarro et al [14]

### Control intervention

The control intervention will be placebo (1 tablet daily per os).

### Concurrent treatments

Iron supplementation will be performed according to usual protocol (note that randomisation will be stratified for centre). Vitamin B and folic acid supplementation are permitted. Melatonin and androgen therapy are proscribed during the study period. If the patient is taking vitamin C, the daily dose will be kept constant throughout the study period. Erythropoietin (EPO) or darbepoetin (DPO) dosages will not be increased during the study, and will only be reduced if haemoglobin levels rise above 125 g/L.

### Blinding

Patients, investigators and outcome assessors will be blinded to the treatment allocation.

### Outcome measures

The primary outcome measure will be the difference in haemoglobin concentration between the oxpentifylline and control groups at the end of the 4 month study period.

Secondary outcome measures include:

a. Difference in the dosage of erythropoiesis stimulating agents (ESA; either erythropoietin or darbepoetin) between the oxpentifylline and control groups at the end of the 4 month study period.

b. Difference in Key's index (ESA dosage divided by haemoglobin concentration) between the oxpentifylline and control groups at the end of the 4 month study period.

c. Difference in frequency of blood transfusion requirements between the oxpentifylline and control groups during the 4 month study period.

d. Occurrence of adverse events in the oxpentifylline and control groups during the 4 month study period.

Exploratory outcome measures that will be studied include the differences in serum concentrations of hepcidin and biomarkers of inflammation (TNF-α, interferon-γ, IL-6 and IL-1) and oxidative stress (isoprostanes, protein carbonyls, plasma catalase and glutathione peroxidase activity) between the oxpentifylline and control groups at the end of the 4 month trial.

### Sample size calculations

Prospective power calculations based on unpaired t-test comparisons indicate that the study will have adequate statistical power (90% probability) to detect a clinically significant increase in haemoglobin concentration of 10 g/L, assuming alpha = 0.05 and a population standard deviation of 12 g/L, if 62 patients were recruited in the study (31 in each group). Allowing for a 5% drop-out rate and a 20% non-compliance rate, we aim to recruit a total of 110 patients (55 in each group) across all centres. We anticipate that this will require a recruitment period of 6 months.

### Statistical analyses

Differences between the intervention and control groups with respect to the primary outcome measure (haemoglobin level at 4 months) will be measured by comparison of the mean haemoglobin in each group, adjusted for baseline values (analysis of covariance). Data will be analysed on an intention to treat basis. For patients withdrawing before the end of the 4 month study, their haemoglobin at the time of withdrawal will be taken as their final haemoglobin. A sub-analysis will be performed to determine whether patients with significantly elevated C-reactive protein (CRP) levels (above the local laboratory's reference range) are more likely to have oxpentifylline-responsive anaemia. The data will be analysed by t-test and by repeated measures analysis of covariance. Because of power considerations and the relatively short duration of the study, no interim analysis is planned.

Secondary analyses will be performed by repeated measures analysis of covariance with and without adjustment for baseline characteristics. The analyses used for secondary outcome measures will include unpaired t-test (Key's index), Mann-Whitney U-test (ESA dosage) and chi square test (blood transfusion requirement, adverse drug reactions).

Categorical baseline characteristics (e.g. sex, race, comorbid illnesses, etc) will be summarized with the number and percent of subjects in each treatment group with the characteristic. Quantitative characteristics (e.g. age and weight) will be summarized by mean and standard deviation or median [interquartile range], depending on data distribution. The number and percent of subjects who are randomized, treated with randomized Study Drug, require intervention, prematurely discontinue, and complete the study will be summarized. Fisher's exact test or the Chi-square test will be used to assess treatment group differences in the proportions of subjects who require intervention and who complete the study. The number and percent of subjects will be summarized for each reason for premature discontinuation.

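### Month-4 ANCOVA is tied to the primary outcome, but the same paragraph adds a t-test and a repeated measures analysis of unspecified data with no stated role

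*Protocol article*

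**What the plan says.** All references are to the protocol article.

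- **Outcome measures** defines the primary outcome without mentioning adjustment: "The primary outcome measure will be the difference in haemoglobin concentration between the oxpentifylline and control groups at the end of the 4 month study".
- **Abstract, Methods/design** gives the same outcome with adjustment: "at the end of the 4 month study period, adjusted for baseline values".
- **Statistical analyses, first paragraph** links one method to the primary outcome by name: "comparison of the mean haemoglobin in each group, adjusted for baseline values (analysis of covariance"). It then covers intention to treat and the handling of withdrawals, and turns to CRP: "A sub-analysis will be performed to determine whether patients with significantly elevated C-reactive protein (CRP) levels" are more likely to respond. The next sentence is "The data will be analysed by t-test and by repeated measures analysis of covariance". The paragraph ends by saying that no interim analysis is planned.
- **Statistical analyses, second paragraph** opens: "Secondary analyses will be performed by repeated measures analysis of covariance with and without adjustment for baseline characteristics".
- **Sample size calculations** uses unpaired t-test comparisons: a 10 g/L difference, SD 12 g/L, alpha 0.05, 90% power, 31 per group, raised to 55 per group.
- **Study design** stratifies randomisation by centre and by disease stage/dialysis type.

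**The concern.** The first paragraph describes the primary analysis, and three methods appear in it. The second and third have no stated role, order or outcome.

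The three do not answer the same question. The t-test at month 4 ignores baseline haemoglobin. A repeated measures ANCOVA, unless a month-4 contrast is named, usually tests the average group difference over all visits. ANCOVA at month 4 is the only one that matches the baseline-adjusted outcome in the Abstract.

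In a phase 3 trial with one primary outcome, the deciding test should be beyond argument before unblinding. If the results disagree, someone who prefers the t-test could point to the unadjusted definition under Outcome measures and to the t-test in the sample size section. Someone who prefers ANCOVA could point to the Abstract and to the opening of Statistical analyses.

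**Working it through.** **1. The plan's own figure.** For a two-sided unpaired t-test, the normal approximation is n per arm = 2 × [SD × (z₀.₉₇₅ + z₀.₉₀) / difference]² = 2 × [12 × 3.2415 / 10]² = 30.3, rounded up to 31. The exact t calculation gives 31.25 per arm, and 89.8% power at 31 per arm. A one-sided 5% test would need 25, so the stated 31 per group (62 in all) is a two-sided 5% t-test calculation. The recruited total also reproduces: 62 / (1 − 0.05 − 0.20)² = 110.2, or 55 per group.

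Powering on a t-test is not an error in itself. If 12 g/L is the SD at a single time point and r is the baseline to month-4 correlation, the ANCOVA residual SD is 12 × √(1 − r²). At r = 0.5 that is 10.4 g/L, so the t-test figure is conservative for ANCOVA. It matters here only because it gives the t-test a second foothold in the document.

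**2. What the sentence could mean.**

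| Reading | For it | Consequence |
|---|---|---|
| All haemoglobin data | It stands in the primary-analysis paragraph, the sentence after it concerns the whole trial, and secondary analyses start a new paragraph | Two further tests on haemoglobin with no stated role |
| CRP sub-analysis only | It directly follows the CRP sentence | The t-test does not fit the question |

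**3. Error rate under the first reading.** Inputs from the article: 55 per arm, baseline plus monthly haemoglobin at months 1 to 4, alpha 0.05. Assumed, because the article does not give them: normal data, no missing values, no treatment effect, and a within-patient correlation of 0.3 to 0.9, either equal between all visits or decaying with time (AR(1)). Repeated measures ANCOVA is taken as the group effect on the mean of months 1 to 4, adjusted for baseline. With 60,000 simulated trials per scenario, the simulation error is about √(0.1 × 0.9 / 60,000) = 0.12 percentage points.

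| Correlation | ANCOVA alone | ANCOVA or t-test | Any of the three | ANCOVA and t-test disagree |
|---|---|---|---|---|
| Equal, 0.3 | 4.9% | 6.2% | 9.7% | 2.7% |
| Equal, 0.5 | 4.9% | 7.2% | 10.2% | 4.6% |
| Equal, 0.7 | 4.8% | 8.2% | 11.1% | 6.5% |
| Equal, 0.9 | 5.1% | 9.4% | 12.3% | 8.6% |
| AR(1), 0.3 | 5.0% | 5.4% | 9.1% | 0.7% |
| AR(1), 0.5 | 5.0% | 5.4% | 8.8% | 0.8% |
| AR(1), 0.7 | 4.9% | 6.1% | 8.7% | 2.3% |
| AR(1), 0.9 | 5.0% | 8.1% | 10.0% | 6.1% |

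Each test alone holds about 5%. Three independent tests would give 1 − 0.95³ = 14.3%; the correlation between these three keeps the figure below that.

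**4. The second reading.** Whether patients with raised CRP respond better to oxpentifylline is a question about a difference of differences: (active − placebo, raised CRP) − (active − placebo, CRP not raised). It involves two factors. A two-group t-test handles one. Run within each CRP group, it gives two separate results and no test between them. Run between CRP groups among treated patients, it has no placebo comparison. A repeated measures model could answer the question with a treatment-by-CRP term, but none is named.

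**The case against.** The strongest reply is that the plan does name its deciding method. ANCOVA is the only method attached by name to the primary outcome, the Abstract agrees with it, and the second paragraph puts repeated measures ANCOVA under secondary analyses. The unclear sentence stands exactly where a method for the CRP sub-analysis would stand. In addition, this is a condensed article, and a formal ranking of analyses commonly belongs in the statistical analysis plan, which is not shown.

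Most of this stands. A reader might infer that the plan never says which test decides, or that its type I error is really 10-11%. The documents support neither. ANCOVA is designated, and the higher error needs a rule that success on any of the three tests counts, which appears nowhere. It also needs a correlation that the article does not give.

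The reply does not dispose of the sentence itself. The point is not a missing ranking: the article states two extra analyses of unidentified data. Calling repeated measures ANCOVA secondary in one paragraph does not settle its role in the other, and the t-test is not labelled for haemoglobin anywhere. If the CRP reading is right, the t-test does not suit its purpose. Either way the wording needs an edit.

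**Conclusion.** The point holds as a minor ambiguity in stated text. As the plan designates it, the month-4 ANCOVA keeps the type I error at about 5%. Only if the other tests could also carry a claim on haemoglobin would it rise, to about 5-9% for ANCOVA or t-test and about 9-12% for any of the three. In the same null simulations ANCOVA and the t-test disagree on significance in roughly 1-9% of trials. These ranges rest on the assumed correlation of 0.3 to 0.9 and on repeated measures ANCOVA being a test of the average over visits. If the sentence belongs to the CRP sub-analysis, the primary test is unaffected, but the t-test named there does not test whether the treatment effect varies with CRP.

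**What to change.** In Statistical analyses:

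- State that the only confirmatory test is the month-4 treatment difference in haemoglobin from ANCOVA, adjusted for baseline haemoglobin and the randomisation strata (at least disease stage/dialysis type), at two-sided 5%.
- Delete the unadjusted t-test of haemoglobin or label it supportive.
- Label the repeated measures analysis of haemoglobin supportive and say that it cannot change the primary conclusion.
- If the sentence was meant for the CRP sub-analysis, say so and replace the t-test with a treatment-by-CRP interaction term in the model.

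The cost is a few lines of text, with no new data and no change in sample size. The price is the loss of fallback analyses: a significant t-test or repeated measures result could not rescue a non-significant ANCOVA.

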## Discussion

This invesigator-initiated, multicentre Australian and New Zealand study has been designed to provide evidence to help nephrologists and their CKD patients better determine whether Oxpentifylline (Trental^®^) administration will safely and effectively treat erythropoietin- or darbepoietin-resistant anaemia. Given that numerous studies have demonstrated that ESA hyporesponsive patients are at significantly increased risk of mortality [28], novel treatments for correcting anaemia in this group (such as with oxpentifylline) may represent an important strategy for improving clinical outcomes. The multicentre nature of the trial will greatly enhance its generalisability. Moreover, the trial sample size has been carefully and prospectively calculated using a minimum clinically important difference in haemoglobin level of 10 g/L and realistic estimates of trial drop-out and non-compliance rates to minimise the risk of a type 2 statistical error. Demonstration of a significant improvement in haemoglobin levels with oxpentifylline therapy will provide clinicians with an important new strategy for effectively treating ESA-resistant anaemia. On the other hand, a negative study will dissuade clinicians from unnecessarily exposing patients to oxpentifylline (which has a small potential for side effects) if it is proven to lack efficacy with respect to treating ESA-resistant anaemia.

